### Safety evaluation

2.8

We will measure blood routine, urine routine, electrocardiogram, liver function, and renal function at baseline and after treatment to evaluate the safety of treatment. Two dedicated researchers will collect any adverse manifestations of patients during the study, including skin pruritus, swelling, necrosis, abnormal bleeding, etc. The details of all adverse events will be recorded in the CRF. The adverse reactions of the 2 groups of patients will be counted at the end of the study. The 2 researchers are unaware of the grouping results.

### Data management and quality control

2.9

All study data will be collected by 1 to 2 research assistants and recorded in the CRF. The research data will be kept in a separate storage room to protect the confidentiality before, during and after the trial. Access to the database will be limited to the researchers of this research group. The ethics committee of our hospital will regularly monitor the progress of the research and ethical norms, and any change in the scheme will be re-approved by the ethics committee.

### Statistical analysis

2.10

The data from this study will be statistically analyzed by independent statisticians through SPSS 18.0 software. The Chi square test will be used for counting data; the mean ± standard deviation ($\bar{\text{x}}\pm \text{s}$) will be used for the measurement data, the independent sample *t* test will be used for the normal distribution, and the Mann–Whitney *U* test will be used for the skew distribution. When *P* < .05, the difference will be considered to be statistically significant.

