#### Diagnostic basis

2.3.1

For the diagnosis of hemorrhoids, refer to the Guidelines for diagnosis and treatment of hemorrhoids in China (2020),^[7]^ and its classification adopts Goligher classification.^[19]^

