### Sample size

2.4

The calculation of sample size is based on the mean and standard deviation of visual analogue scale (VAS) scores at rest 24 hours after operation. According to the results of the pilot study, the sample size in the treatment group is 3.71 ± 1.67 and that in the control group is 4.61 ± 1.47. Set up α = 0.025, 1-sided test, β= 0.10. It is calculated by PASS 15.0 software that 66 participants are needed in each group, and the estimated withdrawal rate is 10%. So 74 patients will be included in each group.

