### Outcomes

2.7

(1)The VAS^[20]^ will be used to evaluate patients’ pain changes. The VAS is often used to measure pain intensity.^[21]^ Patients will be asked to mark a point between 0 and 100, where 100 indicate maximum pain (rightmost end) and 0 indicates no pain (leftmost end). VAS scores at rest will be recorded at 4 hours, 12 hours, 24 hours, and 48 hours after operation for both groups. VAS score of patients during defecation will be recorded on the 1st, 2nd, 3^rd^, and 7th day after operation;(2)The total amount of nimesulide dispersible tablets (tablets) will be taken orally within 7 days after operation;(3)The patient's postoperative stay in hospital (define as the day of operation started to the key of discharge);(4)In the first month of postoperative follow-up, the anal pad tissue samples of the patient will be collected according to the wishes of the patient, and fibulin-3 and fibulin-5 in fibulin protein family will be detected by Western blot;(5)The patients will be followed up in the first month, the third month and the sixth month after operation. The healing or recurrence of hemorrhoids will be evaluated by rectal endoscopy and patient symptoms (including pain, pruritus, bleeding, etc).

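### Section 2.10 lets the distribution choose between unadjusted tests of the 24-hour rest VAS, so the tested quantity may not be the mean difference behind the sample size, and Goligher grade goes unused

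*Protocol article*

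**What the plan says.** Section 2.10 lists three tests: chi-square for counts, and for measurements an independent-samples t "test will be used for the normal distribution" or a Mann–Whitney U test if the distribution is skewed. Measurement data are summarised as mean and standard deviation. No default, criterion for normality or covariate is given.

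Section 2.4 bases the sample size on "visual analogue scale (VAS) scores at rest 24 hours after operation". It gives pilot means and SDs ("the sample size in the treatment group is 3.71 ± 1.67 and that in the control group is 4.61 ± 1.47") and the design settings ("Set up α = 0.025, 1-sided test, β= 0.10").

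Grade II or III is an entry criterion (section 2.3.2), and section 2.3.1 says that "its classification adopts Goligher classification". Section 2.5 describes 1:1 allocation and does not mention grade.

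Section 2.7 says the scale is meant to assess changes in pain. The rest readings are as follows: "VAS scores at rest will be recorded at 4 hours, 12 hours, 24 hours, and 48 hours after operation for both groups". The defecation readings are on days 1, 2, 3 and 7. All are postoperative.

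**The concern.** There are two linked matters.

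**The tested quantity is not fixed.** A t test compares means. A Mann–Whitney test compares ranks and does not in general test a difference in means. Section 2.4 plans for a mean difference, yet section 2.10 lets the test of that outcome become a rank comparison. Because measurements are summarised as means and SDs either way, a rank P value could stand beside a mean difference that it does not test. The choice could also differ among the eight VAS readings.

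**A baseline variable already in hand is not used.** Grade is a plausible predictor of postoperative pain. If it does predict pain, adjusting for it narrows the confidence interval at no cost in patients. A preoperative VAS could do the same, but none is scheduled, and it cannot be recovered after the operation.

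**Working it through.** **1. The plan's own figure.** Inputs from section 2.4: means 3.71 and 4.61, SDs 1.67 and 1.47, one-sided α 0.025, power 0.90.

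- Difference: 4.61 − 3.71 = 0.90
- Pooled SD: √[(1.67² + 1.47²)/2] = √2.475 = 1.573
- Standardised difference: 0.90/1.573 = 0.572
- Normal approximation: n = 2(1.960 + 1.282)² × 2.475/0.90² ≈ 64.2, so 65 per arm
- Noncentral t: power 0.899 at 65 and 0.904 at 66, so 66 per arm
- Withdrawals: 66/0.90 = 73.3, so 74 per arm

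Both stated figures reproduce with an unadjusted t test ("66 participants are needed in each group, and the estimated withdrawal rate is 10" per cent; "So 74 patients will be included in each group").

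**2. What one covariate would add.** In a linear model with arm and one covariate, the residual SD is 1.573 × √(1 − R²) with 2n − 3 degrees of freedom. R² is the share of within-arm VAS variance that the covariate explains. The article does not give it, so a range is assumed. The last column is the grade II to III shift in VAS that would produce each R² if half the patients were grade III (also assumed). It follows from R² = 0.25g²/1.573², that is g = 2 × 1.573 × √R².

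| Assumed R² | Power at 66 per arm | n per arm for 90% power | Implied grade shift g |
|---|---|---|---|
| none (t test) | 0.904 | 66 | – |
| 0.01 | 0.906 | 65 | 0.31 |
| 0.05 | 0.917 | 62 | 0.70 |
| 0.10 | 0.930 | 59 | 0.99 |
| 0.20 | 0.954 | 53 | 1.41 |

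The shifts are in section 2.4's VAS units. An R² of 0.10 from grade alone would need a grade effect of about 1 point, slightly more than the 0.90 sought between treatments. A preoperative VAS correlated 0.3 to 0.5 with the 24-hour score (assumed) would have R² of 0.3² = 0.09 to 0.5² = 0.25. The two covariates may overlap, so their gains should not be added.

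**3. What switching the test does.** The plan gives no criterion, so the check assumed Shapiro–Wilk at 0.05 in each arm: t if both pass, otherwise Mann–Whitney. There were 4,000 simulated trials per scenario, with 66 per arm, two-sided 0.05, and a pure shift of 0.90 for power.

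| Distribution | t test chosen (no effect) | Type I error, switching | Type I error, always t | Power, switching | Power, always t |
|---|---|---|---|---|---|
| Normal | 89% | 0.050 | 0.050 | 0.910 | 0.912 |
| Moderate skew (gamma, shape 4) | 3% | 0.050 | 0.048 | 0.935 | 0.902 |
| Stronger skew (gamma, shape 2) | 0% | 0.053 | 0.048 | 0.967 | 0.898 |

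Simulation error on the type I figures is about ±0.007. Switching does not visibly inflate the error rate, and keeping the t test under skew does not either. What changes is the quantity tested: in these scenarios it was the mean difference in anything from 89% of trials to none.

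**4. Chance imbalance in grade.** With 66 per arm and 30% to 50% of patients grade III (assumed), the 95% range of imbalance is 1.96 × √[2p(1 − p)/66], or about ±16 to ±17 percentage points. If grade shifted VAS by 0.5 to 1.0 point, an imbalance at that edge would move the estimate by about 0.08 to 0.17. The standard error of the treatment difference is 1.573 × √(2/66) = 0.27.

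**The case against.** The strongest reply is that nothing here is invalid. An unadjusted comparison in a randomised trial is unbiased on average, and it is the analysis for which the trial was sized. Choosing t or Mann–Whitney by distribution is conventional, particularly when the outcomes include tablet counts and length of stay. Covariates are often named in an analysis plan, which is not shown here. All of this stands, except that section 2.10 is not merely silent: it states a rule, and that rule leaves the effect measure for the sizing outcome open.

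A second reply also has weight. Under skew with a pure shift, the rank test had more power (0.935 against 0.902, and 0.967 against 0.898). Holding to a linear model gives up that advantage, and a weak covariate would not restore it. The case for one model is then that the result answers the question in section 2.4, not that it has the most power under every distribution.

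Stronger readings are tempting, but the documents do not support them:

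- *Chance imbalance in grade biases the result.* It does not on average, and the unadjusted standard error already covers it.
- *Material precision is certainly lost.* No figure in the article shows how strongly grade predicts pain.
- *The switching rule inflates false positives.* The simulations show no sign of it.
- *A missing baseline makes the VAS outcome uncomputable.* Changes in pain can mean the course after operation, and section 2.4 compares 24-hour levels, which need no baseline.

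**Conclusion.** The point holds as an improvement to the effect measure and efficiency, not as a correction of bias. Section 2.10 leaves it to the distribution whether 24-hour rest VAS is tested as a mean difference or by ranks, while section 2.4 plans for a mean difference. Grade is available for every patient and unused. The planned test is valid, and 66/74 per arm stands.

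The size of the efficiency gain is conditional. It is about 0.3 to 1.4 percentage points of power if R² is 0.01 to 0.05, and about 3 to 5 points if it is 0.10 to 0.20. These figures assume roughly normal residuals, a linear covariate effect and the pilot SDs. No fault is shown in the chi-square test for recurrence, and no change to it is suggested.

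**What to change.** Prespecify one linear model for 24-hour rest VAS with arm and Goligher grade. Report the adjusted mean difference with its 95% CI, remove the normality-based switch for this outcome, and keep Mann–Whitney as a sensitivity analysis only. This changes wording only: grade is already recorded and no patients are added.

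Optionally, record one rest VAS mark before operation and add it to the model, at the cost of one extra mark per patient. If it is not collected, reword section 2.7 so that the VAS is said to follow the postoperative course of pain.

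### No outcome is named primary, and one P < .05 rule covers up to 15 comparisons, while error rate and power are set only for rest VAS at 24 hours

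*Protocol article*

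**What the plan says.** **Section 2.4 (Sample size)** bases the calculation on "visual analogue scale (VAS) scores at rest 24 hours after operation". The error settings are "Set up α = 0.025, 1-sided test, β= 0.10", and the result is that "66 participants are needed in each group, and the estimated withdrawal rate is 10"%, raised to 74 per group.

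**Section 2.7 (Outcomes)** gives five numbered items without a primary or secondary label. The first is pain: "VAS scores at rest will be recorded at 4 hours, 12 hours, 24 hours, and 48 hours after operation for both groups", plus VAS during defecation on four postoperative days. The others are nimesulide tablets over 7 days, length of postoperative stay, fibulin-3 and fibulin-5 in anal pad tissue, and healing or recurrence at months 1, 3 and 6.

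**Section 2.10 (Statistical analysis)** assigns a chi-square, t or Mann–Whitney test by type of data. It then closes with one threshold, P < .05, at which "the difference will be considered to be statistically significant". It sets no order among the outcomes and does not say whether P is one-sided or two-sided.

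**The concern.** The sample size section and the analysis section describe different decisions. In 2.4 there is one comparison, with a 2.5% chance of wrongly favouring Shaobei and 90% power. In 2.10 there are many comparisons, each of which may be called significant on its own at the same threshold. Nothing in 2.7 or 2.10 gives rest VAS at 24 hours a deciding role.

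The gap matters because the article offers more than one idea of success. The sample size points to early pain. The Discussion treats relief of symptoms as the proper yardstick for haemorrhoid treatment and presents the 6-month recurrence comparison as a way to find the best scheme. The abstract and section 2.1 put fibulin expression beside efficacy. If 24-hour pain showed no difference, the text as it stands would not prevent a significance claim on another pain time, on hospital stay or on recurrence. Which outcome decides the trial is a protocol-level choice, and it loses credibility if made after results are seen.

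**Working it through.** **1. Reproduce the plan's sample size.** Inputs from 2.4: treatment 3.71 (SD 1.67), control 4.61 (SD 1.47), one-sided α = 0.025, β = 0.10.

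- Difference: 4.61 − 3.71 = 0.90.
- Common SD: √[(1.67² + 1.47²)/2] = 1.573.
- Normal formula: n = 2 × 1.573² × (1.960 + 1.282)² / 0.90² ≈ 64.2, so 65 per group.
- Exact noncentral t (equal variance or Welch): 66 per group, power 0.903. This matches the plan.
- Withdrawal: 66 / 0.90 = 73.3, so 74. This also matches.

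**2. Check the side of the test.** A two-sided test at 0.05 and a one-sided test at 0.025 use the same critical value, 1.96, and both give 65 by the normal formula. A one-sided test at 0.05 would give 53, and a two-sided test at 0.025 would give 76. Only the first pair fits the stated 66.

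**3. Count the comparisons in 2.7.** Rest VAS 4 + defecation VAS 4 + tablets 1 + stay 1 + fibulins 2 + recurrence visits 3 = 15. Safety data in 2.8 are not counted. Fifteen is an upper reading, because 2.7 says when data are recorded and 2.10 does not say that every time point gets its own test.

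**4. Chance of at least one P < .05 when all 15 nulls are true.** Each test is two-sided at .05.

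- Independent tests: 1 − 0.95^15 = 53.7%.
- Independent tests, at least one favouring Shaobei: 1 − 0.975^15 = 31.6%.

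The article gives no correlations between outcomes, so those below are assumptions. The figures come from simulated normal test statistics (200,000 or more draws).

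| Assumed correlation | Any P < .05 | Favouring Shaobei |
|---|---|---|
| 0.3 between all 15 | 46% | 23% |
| 0.5 between all 15 | 36% | 18% |
| 0.7 between all 15 | 26% | 13% |
| 0.9 between all 15 | 14% | 7% |
| Within related outcomes 0.5–0.8, between them 0.1–0.2 | 33–44% | 17–23% |
| Pain, tablets and stay at 0.3, 0.5 or 0.8; fibulins 0.5; recurrence visits 0.6; none between these groups | 48%, 43%, 34% | 26%, 23%, 18% |

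**5. A narrower count.** Leave out the two fibulins as mechanistic and count recurrence once: 15 − 2 − 2 = 11. Under independence, 1 − 0.95^11 = 43%.

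**The case against.** The best reply is that the intended primary outcome can be inferred. Section 2.4 singles out one measure at one time, and VAS comes first in the outcome list. Section 2.10 gives an ordinary definition of significance; it does not say that superiority may be claimed on any outcome. The full protocol or a statistical analysis plan may hold multiplicity rules. The fibulins are described as mechanistic, and the repeated pain scores are surely correlated, so 15 independent tests is an extreme picture.

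Part of this stands. The absence of an adjustment procedure is not the point here, and neither Holm adjustment nor a repeated-measures model is needed. Separate tests at fixed times are not an error. The 53.7% figure is a ceiling that needs independence, so a chance positive cannot simply be called likely. What does not stand is the appeal to inference. The deciding outcome should be stated, the Discussion supplies rival candidates, and the rule that is written down makes no distinction between outcomes.

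A reader might also infer that 2.10 contradicts 2.4 on sidedness, so that a one-sided test judged at .05 doubles the planned error to 5%. The article does not support that. Section 2.10 states no side. The usual two-sided reading agrees exactly with 2.4 and with the 66 per group, whereas one-sided .05 would have needed only 53.

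**Conclusion.** The concern holds as a mismatch between the stated rule and the planned error control. With no primary outcome named and one threshold for everything, the chance of at least one false positive exceeds 5% in every scenario tried: 53.7% under independence, and about 14% to 48% under the assumed correlations. The share favouring Shaobei is about half of that in the correlated cases (7% to 26%) and 31.6% under independence, against the 2.5% planned in 2.4.

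These figures assume that all 15 comparisons are tested separately and that no true difference exists on any of them. The correlated figures also rest on correlations that the article does not give. The main conclusion does not depend on the exact count, since 11 comparisons still give 43% under independence. The sample size is sound, and the unstated side in 2.10 is an ambiguity only.

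**What to change.** In sections 2.7 and 2.10:

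- Name VAS at rest 24 hours after operation as the primary outcome.
- State that it is tested two-sided at 0.05, which has the same critical value as the one-sided 0.025 in 2.4. This also settles the unstated side.
- State that superiority is claimed on this test alone.
- Label all other outcomes secondary or exploratory and report them as differences with 95% confidence intervals.

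This costs a few sentences and leaves 66 and 74 per group as they are. The downside is that fewer outcomes can support a confirmatory claim. A Bonferroni correction over all 15 comparisons is not needed. At 0.05/15 = 0.0033 it would take 109 per group by the normal formula, and 66 per group would have about 64% power. The change should be made before any unblinded results are seen.

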## Discussion

3

Although there are many treatment schemes for hemorrhoids, the treatment objectives are the same. The guideline points out that the purpose of hemorrhoids treatment is to reduce or eliminate symptoms rather than cure them. Eliminating hemorrhoids symptoms is more meaningful than eliminating hemorrhoids, and should be regarded as the standard of treatment effect.^[22]^ Injection therapy has the advantages of small injury, rapid recovery, and simple operation, which is easy to be favored by doctors and patients. However, there are many kinds of injections, and the safety is not very consistent. We must be very careful in the selection of injections.

Shaobei injection is a traditional Chinese medicine extract, which is mainly composed of citric acid, gallic acid, and paeoniflorin. Citric acid and gallic acid have the effects of acid astringency, astringency and hemostasis, and paeoniflorin has the effects of anti-inflammatory and anti-fibroproliferation.^[23]^ Experimental studies have found that Shaobei injection can effectively reduce local tissue inflammation and edema by inhibiting the release of inflammatory factors by inflammatory cells, and promote the repair and regeneration of mucosal epithelial layer.^[24]^ Clinical studies have found that Shaobei injection therapy can effectively treat grade I–III hemorrhoids, with a cure rate of 100%, the complete atrophy rate of hemorrhoids after 7 days is 95%, and the cure rate after half a year of follow-up is 94.4%.^[25]^ However, there is no standard randomized controlled study to verify these conclusions. This study will take the classic minimally invasive surgery scheme and RBL as the control group to explore the efficacy and safety of Shaobei injection in the treatment of grade II–III hemorrhoids, and we also pay attention to the expression of fibulin-3 and fibulin-5 in fibulin protein family, in order to explore the potential mechanism of Shaobei injection in the treatment of hemorrhoids. Previous studies have found that the recurrence rate of RBL is high.^[9]^ This study will also compare the recurrence of 2 postoperative symptoms through 6-month follow-up, hoping to obtain an optimal treatment scheme.

There are also some deficiencies in this study: firstly, due to the limitations of intervention measures, this study cannot be double-blind, which may cause bias to the results; Secondly, although our follow-up time is 6 months, it may not be enough to pay attention to the recurrence indicators of patients; Thirdly, we need to detect the expression of fibulin-5 protein by taking the tissue expression of anal pad again, which may lead to the loss of follow-up of some patients.
